## Abstract

**Background:**

There is a need to build the evidence base of early interventions to promote children’s health and development in the UK. Chance UK is a voluntary sector organisation based in London that delivers a 12-month mentoring programme for primary school children identified by teachers and parents as having behavioural and emotional difficulties. The aim of the study is to determine the effectiveness of the programme in terms of children’s behaviour and emotional well-being; this is the primary outcome of the trial.

**Methods/Design:**

A randomised controlled trial will be conducted in which participants are randomly allocated on a dynamic basis to one of two possible arms: the intervention arm (*n* = 123) will be offered the mentoring programme, and the control arm (*n* = 123) will be offered services as usual. Outcome data will be collected at three points: pre-intervention (baseline), mid-way through the mentoring year (c.9 months after randomisation) and post- mentoring programme (c.16 months after randomisation).

**Discussion:**

This study will further enhance the evidence for early intervention mentoring programmes for child behaviour and emotional well-being in the UK.

**Trial registration:**

Current Controlled Trials ISRCTN47154925. Retrospectively registered 9 September 2014.

## Background

Longitudinal research indicates that serious anti-social behaviour in adolescence and adulthood can be predicted by early signs of behavioural and emotional difficulties in childhood [1]. Individual-level risk factors for anti-social behaviour often express themselves as impulsiveness, difficulties in relating well to peers, poor problem-solving skills and an inability to regulate conduct and emotions [2, 3]. Left untreated, childhood behavioural and emotional difficulties, which affect approximately 10% of children aged 5–15 in Britain [4], elevate children’s risk for poor outcomes across multiple domains, including academic achievement, health, social relationships and offending [5–11]. It is therefore important to address selected individual and family risk factors in order to prevent behavioural and emotional difficulties in childhood and avert later anti-social and criminal behaviour.

### Realising ambition

Programmes that have been developed and tested in the US dominate the evidence base on what works to divert children and young people away from pathways into anti-social behaviour and crime. The UK is home to many innovative programmes, particularly in the charity sector, but few of these programmes have undergone the level of robust evaluation necessary to determine their impact on children’s outcomes [12]. In the light of several recent examples of programmes imported from the US proving to be largely ineffective in the UK [13, 14], it is important to develop home-grown interventions and test their effectiveness.

The Big Lottery Fund’s Realising Ambition programme seeks to build the evidence base for what works to prevent youth offending in the UK by funding the replication of home-grown and imported interventions with either proven or preliminary evidence of impact on child outcomes [15]. It involves a £25m investment over 5 years (2013–2017) in a portfolio of 25 interventions that are designed to intervene early in order to divert children and young people aged 8–14 away from pathways into crime. Chance UK’s early intervention mentoring programme for children aged 5–11 years with behavioural difficulties has been delivered in London for over 20 years and is one of the interventions selected for inclusion in the Big Lottery Realising Ambition portfolio.

### Mentoring to improve child outcomes

Mentoring programmes typically involve a supportive relationship between a child and positive adult role model who enables the child to take part in positive activities and make a commitment to socially appropriate goals. It is theorised that this contributes to children’s social-emotional, cognitive and identity development and that this acts as the mechanism through which mentoring has the potential to improve developmental outcomes, including behaviour [16].

Meta-analytic reviews indicate that mentoring typically reduces conduct problems, aggression and substance use [17, 18]. There are also reported improvements in educational achievement, social competence and emotional well-being [19–21]. Meta-analyses of mentoring programmes find an average effect size of 0.2 for young people’s behavioural and emotional outcomes [21, 22]. Typically, evaluations focus on mentoring interventions for adolescents and examine distal outcomes, or long-term consequences, such as reoffending and school grades.

The best-known and most frequently evaluated mentoring programme is Big Brothers Big Sisters of America (BBBSA), a community-based mentoring programme for disadvantaged 10–14 year-old children at risk of academic disengagement. BBBSA matches children to a volunteer adult, who is of the same gender and shares the same interests and goals as the mentored child, for at least 12 months of one-to-one mentoring. Randomised controlled trial (RCT) evaluations in the US demonstrate the effectiveness of BBBSA in improving behavioural and academic outcomes. For instance, mentored young people were 32% less likely to report hitting somebody during the previous 12 months, reported skipping 52% fewer days of school than non-mentored young people, and reported moderately better school grades (3% higher) than the control group [23, 24]. Additionally, mentored young people from minority ethnic backgrounds were 70% less likely to report initiating drug use [23, 24]. Furthermore, an RCT of Big Brothers Big Sisters in Ireland found that young people with a mentor felt more supported, showed more prosocial behaviour, and had a greater sense of hopefulness for the future than non-mentored young people [25].

While there are many variations of mentoring interventions, meta-analyses and research reviews have identified at least six features that are common to effective programmes. The first is matching the young person with the correct mentor [21, 22, 26–28]. A match based on shared interests (for example supporting the same football team) may make the young person more responsive to the adult’s guidance and advice, since those who perceive a high level of similarity tend to have higher-quality and longer-term relationships with their mentors. Second, mentoring programmes are more effective when there are structured activities planned, particularly ones that are driven by the needs and interests of the young person [21, 22, 26, 27]. Third, programmes targeted towards young people who are demonstrating behavioural difficulties tend to show greater impact than universal interventions [21, 22, 26]. Fourth, parent support and involvement in the programme is also beneficial [22, 26]. Fifth, the longer the mentoring relationship lasts, the better the outcome; relationships lasting for 12 months or longer have a more positive impact [26]. Sixth, the frequency of contact matters: one review found that programmes encouraging mentors and young people to meet at least once a week were more successful [17]. It is important for mentors to be clear about the frequency and duration of contact as this stops unrealistic expectations and allows a trusting, stable relationship to be built [22].

Although not researched as thoroughly, there are elements of mentoring programmes that reduce the chances of success. The main problem is a mismatch between the mentor and the young person [29]. Matching mentors and young people solely on the basis of race or ethnicity (something which often occurs) is not associated with improved outcomes [21]. Relationships that last for under 3 months can actually have a negative effect on young people’s confidence and self-worth [26]. Lack of mentor training and expertise has also been shown to decrease the effectiveness of mentoring [29].

### Chance UK’s early intervention mentoring programme

Chance UK’s mentoring programme is for children aged 5–11 years who are reported to be displaying challenging behaviour and emotional problems at school and at home. It is designed to intervene early in the development of such problems and aims to prevent future antisocial and criminal behaviour by reducing associated risk factors (such as early problem behaviour, lack of a positive role model, and limited opportunities) and by promoting children’s strengths (such as decision-making and coping skills, social skills, and competencies such as academic, sporting or creative abilities). Chance UK uses a solution-focused approach [30, 31] to improve children’s behaviour throughout 1 year of one-to-one mentoring by trained, supervised volunteers. The programme’s core design is in line with the features of effective mentoring programmes identified by meta-analyses and research reviews: Chance UK only serves children with an identified level of need; volunteer mentors are highly trained to deliver a tailored programme of structured activities; a thorough matching process – based on the mentor’s personality and characteristics – is designed to create successful matches; the sessions take place weekly for 1 year; and parents are offered support as part of the programme. As such, it is reasonable to expect that Chance UK’s programme will have an effect size that is greater than the average cited above.

Other aspects of Chance UK’s programme are different from mentoring programmes that have been evaluated previously by RCT or quasi-experimental design studies. In particular, it works with a younger age group than typical mentoring programmes, so a greater impact may be expected as younger children’s behaviour may be more malleable before negative behaviours become embedded [32, 33]. Chance UK’s programme also focuses on achieving more proximal outcomes, or short-term consequences, such as better behaviour via improvements in self-esteem and self-efficacy, rather than targeting distal outcomes such as delinquency and school grades that are the typical focus of mentoring programmes. Generally, interventions have stronger effects on proximal than distal outcomes [34]. Together, these factors suggest that the Chance UK programme will produce a higher effect size than is typically found in evaluations of mentoring programmes.

The Chance UK mentoring programme was previously evaluated in a pre-post study involving 100 children who had received mentoring [35]. This evaluation looked at changes in the level of children’s behavioural and emotional functioning from the beginning to the end of the programme. The parent-rated Strengths and Difficulties (SDQ) Total Difficulties score was available for 99 children entering the programme; on average this score was 19.25 out of 40 (within the ‘abnormal’ range (≥17) in the three-band classification of SDQ scores: www.sdqinfo.com). After a year of mentoring, the scores for 92 children who had data available decreased to an average of 14.82 out of 40 (within the ‘borderline’ range of difficulties (scores of 14–16), a statistically significant improvement (t_(91)_ = 7.15, *p* < 0.001). The average teacher-rated SDQ Total Difficulties scores decreased from 23.41 to 16.48 (t_(85)_ = 8.07, *p* < 0.001).

Building on this preliminary evidence, this paper describes the protocol for an RCT evaluating the Chance UK mentoring programme.

## Methods

### Objectives

The objectives of the trial are:To estimate whether offering the Chance UK mentoring programme has an effect on children’s behaviour and socio-emotional well-being in comparison to similar children who were not offered the programme.To estimate whether the Chance UK mentoring programme has an effect on children’s self-esteem and self-efficacy, both of which are hypothesised mediators in the programme’s theory of change.To describe the extent to which the Chance UK mentoring programme is implemented with fidelity to the programme design.

It is hypothesised that, when compared with children who were not offered mentoring (the control arm), children who are offered the mentoring programme (the intervention arm) will, at follow-up, demonstrate fewer emotional and behavioural difficulties (as reported by parent/carers) and higher self-esteem and self-efficacy (self-reported by children who were aged 8 years or above at baseline).

### Design

A two-arm, randomised controlled, parallel group, superiority trial will be conducted to evaluate the effectiveness of Chance UK’s mentoring programme in improving behavioural and emotional outcomes in primary school children who have teacher- and parent/carer-reported behavioural difficulties. The intervention arm will be offered the mentoring programme; both trial arms will have access to services as usual. Assessments will take place pre-intervention (baseline), mid-way through the mentoring year (c.9 months after randomisation, midpoint) and post- mentoring programme (c.16 months after randomisation, endpoint). (See Fig. 1 for an overview of assessments.)

**Fig. 1 Fig1:**
[figure not shown]
Trial timeline

### Setting

The intervention will be delivered by Chance UK in a range of settings in the community in five boroughs of London, UK: Enfield, Hackney, Islington, Lambeth and Waltham Forest. Participants must live or attend school in one of these boroughs at the time of recruitment. The control group will come from the same population. Assessments for the RCT will take place in the home and school (online for teachers).

### Participants

Children are eligible to participate in the study if *all* of the following criteria are satisfied:The child is aged between 5 and 10 years old when referred to the project (meaning the child will be aged 5–11 while receiving mentoring).The child lives or attends school in any of the London boroughs of Enfield, Hackney, Islington, Lambeth or Waltham Forest.The child scores ≥16 on teacher-reported SDQ Total Difficulties (indicating that the child is in the ‘abnormal’ range).The child scores ≥14 on parent/carer-reported SDQ Total Difficulties (indicating that the child is in the ‘borderline’ (scores of 14–16) or ‘abnormal’ (scores of 17–40) range).Both parent/carer and child are willing to take part in the programme and the study (school staff understand that referral to the intervention constitutes referral to the study).There is no diagnosis of autism or any developmental delay that would prevent the child from engaging in the programme and the study, as identified through school records and parent report.There is no known risk of violence towards Chance UK staff or the research team by the child or parent/carer.The child does not have a sibling enrolled in the study.

### Recruitment and retention

Recruitment will take place between May 2014 and February 2016. Children will be referred to the trial by a member of school staff who knows the child well (e.g. a class teacher or Special Educational Needs Coordinator (SENCO)) and who has concerns about the child’s behaviour. Chance UK has well-established relationships with many primary schools in five London boroughs in which the service has been operating, and will be responsible for sourcing referrals from schools. New schools may be approached as part of Chance UK’s organisational strategy. Chance UK estimates that approximately 65 schools could potentially make a referral during the study period.

Analysis of a sample of Chance UK’s archive referral data suggests that around 5% of referrals will be ineligible based on criteria such as the child having autism spectrum disorder and/or developmental delay or the family being unsuitable for the programme. Of the remaining cases, about 10% will reach the ‘abnormal’ cut-off (≥16) on the teacher-rated Strengths and Difficulties Questionnaire [4]. The Chance UK case analysis showed that only 70% of teacher-rated eligible children also reach the eligibility threshold of the ‘borderline’ cut-off (≥14) on the parent/carer-rated SDQ. It is also assumed, based on a previous evaluation of a mentoring programme [36], that approximately 10% of the families who are referred and eligible will not be interested in taking part in the study and will not complete the baseline assessment. Chance UK must over-recruit to take these factors into account.

Communications about the research study will be distributed to schools directly by Chance UK and posted online alongside the referral form on Chance UK’s website. In particular, an information leaflet for school staff will be provided to explain the details of the research study and to make clear that during the recruitment phase of the study any referral to the service constitutes a referral to the research study.

Chance UK will screen each completed referral form, which contains the teacher-rated SDQ, to check eligibility for the research study. Provided that the child’s main parent/carer provides verbal consent to the referrer and the referrer gives written consent for this data to be shared with the research team, each suitable referral will be passed to the Trial Coordinator at Dartington Social Research Unit (DSRU) who will contact the main parent/carer by telephone to explain more about Chance UK’s programme and the research study, and to conduct further eligibility checks, including the baseline parent-rated SDQ. Where parents/carers are interested in their child participating and the child meets the initial eligibility criteria, an appointment will be made for an independent data collector to visit the family home to obtain written informed consent and collect additional baseline measures prior to randomisation.

Several strategies designed to minimise the level of attrition from the trial will be put in place. First, efforts will be made during the consent process and via information leaflets to make sure that participants are fully aware of what the research study involves and what will be expected, and to emphasise the value of taking part in the study. Second, the trial has been branded the ECHO project (Evidence for CHildren’s Outcomes) and will be communicated in a professional and attractive way that participants will be more likely to identify with and be interested in. Third, participants will be provided with change of address cards to notify the research team of new contact details. Fourth, efforts will be made to keep participants engaged in the study between data collection time points by sending a regular newsletter on the progress of the trial and a birthday card for the child. Fifth, families will be offered a small monetary incentive (shopping vouchers valued at £10) for each of the three home data collection appointments to compensate for their time spent in completing the questionnaires. Finally, Chance UK will work to keep school staff engaged and to support referrals to the project.

Should intervention group participants wish to withdraw from the mentoring programme, they will be encouraged to remain engaged in the research study by continuing to provide outcome data during assessment periods. Parents/carers will be informed of their right to withdraw their child from the research study at any time without giving any reason and with no adverse consequences; withdrawing from the study would not affect provision of the mentoring programme for the intervention group. Where parents/carers wish to fully withdraw their child from the study, *all* data collection for this case will cease (i.e. data will no longer be collected from teachers for the child). All previously collected data relating to this child will stand unless the parent/carer also asks for all them to be removed from the dataset (this can be done up to the point that data are analysed). Data collection with all participants will be completed voluntarily. Where parents/carers, school staff or children (aged 8–11) decline to complete a data collection point or request to withdraw themselves only, the assessments with the other reporters may still take place. For instance, a teacher may withdraw from the study but the assessments with the parent/carer and the child may continue, or the parent/carer may decline to complete a data collection point but data will still be collected from the teacher.

### Sample size

Recruitment of 246 eligible children to the project will allow detection of an effect size of 0.4 at *p* < 0.05 with 80% power (an effect size of 0.4 requires a minimum sample size of 99 participants per arm) and allows a study drop-out rate of up to 20%.

### Randomisation

A computer-generated randomisation sequence will be used to assign the participants to the intervention and control arms in a 1:1 ratio. Separate randomisation lists will be created for each site (Enfield, Hackney, Islington, Lambeth and Waltham Forest). In each location the first 25% of children will be allocated by simple randomisation and thereafter minimisation will be used to reduce imbalance between the programme and control groups in terms of age (< 9 versus ≥9 years) and gender (male versus female; the authors are not aware of any best practice recommendations on how to balance allocation for non-binary genders). Randomisation will take place after baseline data collection with families. The randomisation approach will be dynamic, meaning that each participant can be randomised as soon as they have completed the baseline assessments. The allocation sequence will be concealed using an online central randomisation service set up and maintained by statisticians at the University of Exeter (RT and TE, neither of whom are able to influence the data or the data analysis) that will conceal the sequence until assignment to group. The randomisation process will require the Trial Coordinator to log into a password-protected website and enter the relevant data of each newly recruited participant in order to receive the allocation.

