### Blinding

Following randomisation, the Trial Coordinator will notify Chance UK, the child’s family and the referrer about the group allocation. The Principal Investigator, Trial Manager, data collectors and statisticians will be blind to participant allocation status. Allocation status will be recorded in a password-protected spreadsheet. The Trial Manager will be informed of allocation status if this is required to respond appropriately to a safeguarding concern (but will not be informed of the research ID for the child unless this is necessary).

Participants will be instructed not to reveal their allocation status to the data collector at the follow-up assessment points. It is considered unlikely that unblinding data collectors at any point in the study will bias the outcome data, as the outcome data are collected using self-completion questionnaires rather than through observation or interview (unless a participant asks the data collector to administer the questionnaires in interview style). After follow-up data collection, the data collector will be asked to report (i) whether they believe they know the allocation outcome and, if so, (ii) which arm they believe it to be and (iii) at which point during the visit they believe they were unblinded. If the data collector indicates that they believe they know the allocation outcome at midpoint, a different data collector will be asked to complete data collection with this family at endpoint (regardless of whether the suspicion is correct).

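### One unblinded role takes the telephone parent SDQ, enters children into a two-factor minimisation and sees every past allocation, so it can guess upcoming allocations better than chance

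*Protocol article*

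**What the plan says.** The protocol article's Randomisation section sets the service to "assign the participants to the intervention and control arms in a 1:1 ratio", with a separate list for each of five boroughs. Within a borough, "In each location the first 25% of children will be allocated by simple randomisation"; "thereafter minimisation will be used to reduce imbalance between the programme and control groups in terms of age" group (under 9 versus 9 and over) and gender. A central online service run by university statisticians hides the sequence until assignment. Entry will "require the Trial Coordinator to log into a password-protected website and enter the relevant data of each newly recruited participant", and that person then receives the allocation.

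Under Recruitment and retention, Chance UK screens the referral form first. The Trial Coordinator then telephones the parent "to conduct further eligibility checks, including the baseline parent-rated SDQ". An independent data collector takes written consent and the remaining baseline measures at home. Randomisation follows completion of baseline.

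Under Blinding, "the Trial Coordinator will notify Chance UK", the family and the referrer of the result. The roles listed as blind are the Principal Investigator, Trial Manager, data collectors and statisticians. The Trial Coordinator is not among them.

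**The concern.** The parent SDQ taken by telephone does two jobs. A score of 14 or more is an entry criterion, and the same score is the baseline of the primary outcome, used as a covariate. The entry gate matters in practice: Recruitment and retention expects only 70% of teacher-eligible children to pass it. The person who takes this score also knows every earlier allocation and each child's borough, age and gender, which are all the inputs that the minimisation uses.

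Concealing a list protects a fixed sequence. It does not prevent someone from working out which arm the running totals favour for the next child. The reassurance about unblinding in the Blinding section concerns data collectors at follow-up and self-completed questionnaires, so it does not cover this stage.

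At stake is selection bias: through how actively a family is pursued, how a borderline telephone score is taken, or the order in which waiting children are entered. The article says that a child can be randomised once baseline is complete, but states no strict order of entry. Baseline adjustment removes only the part of such bias that is measured.

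**Working it through.** The article gives no figure for predictability, so there is none to reproduce. The check is a simulation of one borough's list.

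**Inputs from the article.** Total 246 children; five boroughs; 1:1 allocation; first 25% per borough by simple randomisation; then minimisation on two binary factors; randomisation from July 2014 to March 2016, which is 21 months.

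**Assumptions.** Equal boroughs (246 / 5 = 49.2, taken as 49 children); 80% boys; 40% aged 9 or over. The probability p of following the favoured arm is not stated, so it was set at 1.0 (deterministic), 0.9, 0.8 and 0.7. Ties are settled by a fair coin.

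**Rule.** For the next child, let S = (intervention children in the same age group + intervention children of the same gender) − (the same sum for control). If S ≠ 0, the arm with the smaller sum is favoured. The observer knows the totals and guesses the favoured arm. If d is the share of allocations with S ≠ 0, then

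share correct = d × p + (1 − d) × 0.5.

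**At the moment of entry (after the run-in).**
- p = 1.0: d = 0.757; 0.757 + 0.243 × 0.5 = 0.88. About three in four allocations are fully determined.
- p = 0.9: d = 0.789; 0.710 + 0.106 = 0.82.
- p = 0.8: d = 0.825; 0.660 + 0.088 = 0.75.
- p = 0.7: d = 0.869; 0.608 + 0.066 = 0.67.

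Simple randomisation gives 0.50. Changing the borough size to 25 or 75, or the age and gender mix, moves these by about 0.01 at most. Counting the run-in as well, the shares at p = 1.0, 0.8 and 0.7 are about 0.79, 0.69 and 0.63.

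**At the telephone call.** The call comes before the home visit, and other children in the borough may be allocated in between. The average rate is 49.2 / 21 = 2.3 children per borough per month, so a lag of one to three children is plausible; the lag itself is an assumption. The observer now guesses from totals that are out of date by that number of children. Percentage correct:

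| p | At entry | 1 intervening | 2 intervening | 3 intervening |
|---|---|---|---|---|
| 1.0 | 88 | 62 | 63 | 58 |
| 0.9 | 82 | 65 | 64 | 60 |
| 0.8 | 75 | 65 | 63 | 61 |
| 0.7 | 67 | 63 | 61 | 60 |

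Repeat runs differ by about one point, so the range at the call is about 58 to 66%. With out-of-date totals, a random element brings no clear gain at the call. Its benefit is at entry.

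**The case against.** The strongest reply is that the article is a condensed account. A random element in minimisation is a detail commonly left to the full protocol or the randomisation specification, so its absence from one paragraph proves nothing. That stands. A reader might infer that minimisation here is deterministic and that most later allocations are known in advance. The article supports neither: it is silent on the probability, and it does not say that the Trial Coordinator knows the algorithm or keeps totals by borough, age and gender.

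Second, most of the feared harm would occur at the telephone call, not at entry, and prediction is weaker there. That stands too, and the range at the call is given separately for that reason. An observer who also forecast the waiting children could do somewhat better than the table shows.

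Third, real safeguards exist. Chance UK makes the first screen. The entry criteria are largely numeric or come from records. A blinded, independent data collector takes consent and the home baseline. Randomisation waits for complete baseline data, and the Trial Coordinator belongs to the research unit, not the provider. These narrow the opening. They do not close it, because the telephone SDQ and the eligibility decision come before the home visit and are in the hands of the role that holds the allocations.

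Fourth, any minimised trial whose coordinator sees past allocations is open to some guessing. True, but here the same person also takes the score that decides entry and serves as the primary-outcome baseline. That overlap is stated in the text and does not depend on the algorithm.

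**Conclusion.** The concern holds as a stated overlap of roles that gives better-than-chance prediction. Under the assumptions above, guesses at entry are right about 67 to 75% of the time with a random element of 0.7 to 0.8, and about 88% only if minimisation is deterministic. At the telephone call they are right about 58 to 66% of the time if one to three same-borough children intervene. The first 25% in each borough are not predictable.

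This shows an opportunity for selection bias. It does not show that bias occurred, and the documents give no ground for saying so. Chance UK, which sources and first screens referrals, is also told each allocation, so a related but weaker exposure exists there; it does not take the parent SDQ. The point is a worthwhile, cheap improvement and not a flaw that undermines the trial.

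**What to change.** 1. Lock the eligibility decision and the telephone parent SDQ score in the system when they are taken, before the home visit.
2. Enter children for randomisation strictly in the order in which they complete baseline.
3. Have the online service send allocation notices automatically to Chance UK, the family and the referrer, so that the person making eligibility calls does not hold the running allocation list. Automatic notices also keep the Principal Investigator and Trial Manager blind.
4. State the probability with which minimisation follows the favoured arm. If it is deterministic, add a random element.

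Items 1 to 3 deal with the overlap of roles whatever the algorithm. Item 4 helps mainly at entry and does not replace them. The cost is a working rule and the set-up of automated notices to three parties. If a random element has to be added, balance on age group and gender will be slightly looser, but the Statistical methods section already adjusts for both.
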